### Organization

#### Monitoring

A data monitoring committee will review accumulating data and make recommendations to the trial steering committee with respect to trial conduct and participant safety. Charters outline the roles and responsibilities of these committees. The data monitoring and trial steering committees will be independent of the sponsor and will have no competing interests. Interim analysis and adverse event data will be performed by the trial statistician and made available to the data monitoring and trial steering committees.

A trial conduct audit will be conducted internally; results will be made available to the data monitoring and trial steering committees. Significant protocol amendments will be made to the NHS Research Ethics Committee, UK Clinical Research Network, ISRCTN trial registry and relevant journals where the protocol is published.

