### Blinding

Trial participants, hand therapists conducting the Total Active Motion assessment, composite flexion and wrist movements, and research nurses administering the Disabilities of Arm, Shoulder and Hand Outcome Measure, Patient Evaluation Measure, visual analogue scales and EuroQol five dimensions questionnaire will be blinded to the method of intervention.

The operating surgeon, clinician assessing for complications at follow-up visits and individuals assessing the patient radiographs will not be blinded.

Blinding will be achieved by only allowing the permissible individuals to have access to the method of fixation information, the operation record and radiographs of the participant.

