### Statistical analysis

Baseline data (e.g. age and sex) will be summarized to check comparability between treatment arms, and to highlight any characteristic differences between those individuals in the study. Standard statistical summaries (e.g. medians and quartiles or means and standard deviations, dependent on the distribution of the outcome) and graphical plots will be presented for the primary and secondary outcome measures.

Differences between treatment groups will be assessed on an intention-to-treat basis. Tests will be two-sided and considered to provide evidence for a significant difference if *P* < 0.05 (5 % significance level). Estimates of treatment effects will be presented with 95 % confidence intervals.

The temporal patterns of any complications will be presented graphically and, if appropriate, a time-to-event analysis (Kaplan–Meier survival analysis) will be used to assess the overall risk and risks within individual classes of complications (e.g. implant failure).

Missing data are not expected to be a problem for this study. If the degree of data loss is relatively low, the primary analysis will be based on complete cases only, with analysis of imputed datasets used to assess the sensitivity of the analysis to the missing data. If the level of missing data is higher than expected, missing data will be imputed using the multiple imputation facilities available in R (http://www.r-project.org/).

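### The interim analysis goes to the trial steering committee as well as the data monitoring committee, with no limit to pooled or masked data

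*Protocol article*

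**What the plan says.** All the text on interim reporting is in the first paragraph of Organization, Monitoring, in the protocol article. It makes four statements in sequence.

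- On roles: "A data monitoring committee will review accumulating data and make recommendations to the trial steering committee with respect to trial conduct and participant safety".
- On where details are kept: "Charters outline the roles and responsibilities of these committees".
- On independence: "The data monitoring and trial steering committees will be independent of the sponsor and will have no competing interests".
- On who receives the output: "Interim analysis and adverse event data will be performed by the trial statistician and made available to the data monitoring and trial steering committees".

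The Blinding section adds a general rule on access to allocation: "Blinding will be achieved by only allowing the permissible individuals to have access to the method of fixation information". It lists who is blinded (patients, hand therapists, research nurses) and who is not ("The operating surgeon, clinician assessing for complications at follow-up visits and individuals assessing the patient radiographs will not be blinded"). The steering committee is in neither list.

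**The concern.** A trial has a separate data monitoring committee so that one small group can look at the comparison while everyone who directs the trial stays unaware of it. The first statement in the Monitoring paragraph sets up that arrangement: one committee looks, and the other receives advice. The last statement sends the interim analysis to both. If the steering committee holds the analysis, it no longer needs to rely on the advice, and its later decisions on conduct can be coloured by knowing which fixation method is ahead.

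What is at stake is the credibility of conduct decisions taken during the trial, such as continuing, extending recruitment or amending the protocol. A reader of the final report could not rule out that these were made with the interim difference in view. The trial already has unblinded radiograph readers for its primary outcome, so keeping the oversight body unaware of interim results is a safeguard worth having.

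**Working it through.** The point rests mainly on reading the text. A short calculation then shows what an interim comparison would look like.

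**1. Who reviews and who is advised.** The opening sentence gives the data monitoring committee the accumulating data and gives the steering committee its recommendations. It gives the steering committee no data.

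**2. Who receives the analysis.** The closing sentence names both committees as recipients of the same material, the interim analysis and the adverse event data. It distinguishes no open from closed report, no pooled from by-arm tables and no masked from unmasked arms.

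**3. Does any other text narrow this?**
- The Blinding section limits access to the fixation method to permitted individuals, but does not say whether steering committee members are among them.
- The Statistical analysis section does not mention interim reporting.
- The charters are cited but not shown.

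Nothing in the document restricts what the closing sentence grants.

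**4. Does independence close the gap?** Independence from the sponsor and the absence of competing interests deal with motive. They do not deal with knowledge of results, which is what the separation in step 1 is for.

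**5. What an interim comparison would show.** Inputs from Sample size: 8 % non-union in each group, 126 evaluable per group, margin 10 percentage points.

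The plan's own figures reproduce. As an equivalence calculation with each one-sided test at 5 % and 80 % power, 2 × 0.08 × 0.92 × (1.645 + 1.282)² / 0.10² ≈ 126 per group (126.06 before rounding the normal quantiles), and 252 / 0.80 = 315.

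The timing of the interim look is not given, so the fraction of patients is an assumption. With n per group at the look:

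SE = √(2 × 0.08 × 0.92 / n) = √(0.1472 / n), and 95 % half-width = 1.96 × SE.

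| Assumed fraction of evaluable patients | n per group | SE (points) | 95 % half-width (points) |
|---|---|---|---|
| one third | 42 | 5.9 | 11.6 |
| one half | 63 | 4.8 | 9.5 |
| two thirds | 84 | 4.2 | 8.2 |

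Over this range the uncertainty is close to the whole 10-point margin or exceeds it. A committee shown the difference would be looking mostly at chance variation. The calculation illustrates why the comparison is better withheld. It does not test any figure in the plan, and the rewording below changes none of them.

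**The case against.** The strongest objection is that the text never says by-arm, comparative or unmasked. What each committee sees, and in what form, is ordinary charter content, and the article points to charters. The steering committee might receive only pooled tables. This stands in part: a reader might infer that by-arm results are stated to go to the steering committee, and the document does not say so. The inference is reasonable in a two-arm trial where both committees are sent the same output, but it remains an inference. It does not remove the point. If the charters do restrict access, the published sentence describes the arrangement wrongly and should be brought into line with them.

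A second objection is that both committees are independent, and that any added bias is small beside primary-outcome readers who are openly unblinded. The comparison of size is fair and keeps the point modest. Independence, however, answers a different question (step 4 of the working).

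Two stronger readings should also be set aside.

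- A reader might infer that the steering committee could use interim knowledge to choose how the four union grades are split, or how missing data are handled. No text gives that committee control over either choice.
- A reader might infer that an interim analysis makes the final test and interval invalid, because the Statistical analysis section says "Estimates of treatment effects will be presented with" 95 % confidence intervals and mentions no adjustment. The document plans no early claim of efficacy, equivalence or non-inferiority, and gives the purpose of monitoring as conduct and safety. Without an early claim, an unadjusted final interval is not wrong.

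**Conclusion.** The point holds as one of wording and access. The Monitoring paragraph makes the interim analysis available to the steering committee without restriction, although the same paragraph has that committee receive advice from the body that reviews the data. As written, the steering committee could know the treatment comparison during the trial.

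This rests on two readings: that an interim analysis in a two-arm trial is, or may be, comparative, and that a committee receiving recommendations on conduct is expected to act on them. Both are natural, but neither is spelled out. The unseen charters could make the practice sounder than the text.

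There is no numerical effect on sample size, power or type I error. It is a cheap improvement and does not by itself threaten the trial's result.

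**What to change.** Replace the last sentence of the first paragraph under Organization, Monitoring with wording to this effect: the trial statistician prepares the interim analysis; comparative results, including adverse events by arm, go only to the data monitoring committee; the steering committee receives that committee's recommendation together with pooled recruitment, follow-up and safety figures. Check both charters and align them if they say otherwise. If they already restrict access in this way, only the protocol sentence needs correcting.

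The cost is a text change in the protocol and possibly in the charters. No patients, visits, data items or analyses are added. The one small downside is that the steering committee must act on a recommendation without seeing the by-arm table behind it.

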## Discussion

The SUBMIT trial is, to our knowledge, the first clinical trial to assess the efficacy of unicortical screw and plate fixation in patients with metacarpal fractures. Unicortical plate and screw fixation of metacarpal fractures is a less technically demanding and quicker procedure with, theoretically, less soft tissue disruption and potentially fewer complications.

Published studies have not proven a superiority of one fixation method over the other in cadaveric models. This study has been designed as a non-inferiority trial. We believe that should this study demonstrate equivalence between unicortical and bicortical fixation, unicortical fixation may become the standard method of fixing metacarpal fractures requiring surgery in the future.

## Trial status

Recruitment commenced in June 2015 and is expected to conclude in May 2018. Additional centres are expected to commence recruitment in 2016. The first results of the study are expected in late 2018.

## Abbreviations

CONSORT: Consolidated Standards of Reporting Trials
CREST: Clinical Research Tool
NHS: UK National Health Service
